## Methods and analysis

### Design

We propose a prospective cluster randomised controlled trial (RCT) evaluating the implementation and effectiveness of intervention strategies for safe PHM. The study is based on a hybrid 2 trial design, where clinical effectiveness and implementation outcome are given equal priority.^24^ The implementation process will be evaluated using a combination of qualitative and quantitative methods, as described in the Medical Research Council guidelines for process evaluations of complex interventions.^25 26^ For reporting this RCT, the study follows the Standard Protocol Items: Recommendations for interventional trials checklist.^27^ The study has taken guidance from the Standards for Reporting Implementation Studies.

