### Intervention effectiveness

#### Primary outcomes

The intervention effectiveness will be measured with regards to the safety climate using NOSACQ-50. This comprises 50 items across seven safety climate dimensions in the workplace (management safety priority, commitment and competence; management safety empowerment; management safety justice; workers’ safety commitment; workers’ safety priority and risk non-acceptance; safety communication, learning and trust in coworkers’ safety competence and trust in the efficacy of safety systems).^32^ The questionnaires are scored on a scale of 1–4, where 1 equals ‘strongly disagree’ and 4 ‘strongly agree’, where a score greater than 3.30 indicates a good safety climate. An additional 14 specific research-based questions to evaluate the safety climate for PHM will also be used in line with previous studies.^6^ These questions involve the dimensions of using equipment, other aspects of safety, performing risk assessment and coproduction between caregivers and patients. They also use a scale of 1–4, where 1 is ‘strongly disagree’ and 4 is ‘strongly agree’, based on the design in NOSACQ-50.^32^

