### Data analysis and statistics

A power calculation was made to estimate the number of clusters and participants in each cluster. The Power calculation was based on the primary intervention effectiveness outcome NOSACQ-50, and a calculated minimum detectable change of 0.7 with an SD of 0.5 and within cluster correlation of 0.7. A power level of 0.8 (80%) and alpha of 0.05 was used. The calculation resulted in at least six care units (clusters) for each arm with a minimum of 15 participants in each care unit. Two predetermined conditions were taken into consideration in the randomisation, size of cluster and regional or municipal healthcare, as this ensured equal randomisation in arm A and arm B.

Quantitative data will be analysed using the IBM SPSS. Descriptive data are presented with mean and SD, median and range or counts and percentages. Comparisons between groups are analysed with an independent sample t test, Mann-Whitney U test or χ^2^ test. Multiple imputation will be used for missing data, and a sensitivity analysis will be made. Potential differences between the intervention arms regarding primary outcome at 4-month and 12-month follow-up will be estimated using linear mixed models for repeated measures. The models will be adjusted for possible confounders (baseline differences concerning age and working experience), and the results will be presented as point estimates with 95% CIs. Care units with a low rate of adherence to the assigned intervention strategy will in a subgroup analysis be compared with care units with high rate of adherence. The limit for statistical significance will be set at α=0.05. All interviews and focus group discussions will be digitally recorded and transcribed verbatim. The transcribed texts will be imported into NVivo V.12 (QSRInternational, Melbourne, Australia) to manage and code data. Qualitative content analysis will be used to analyse the data.^49^ A deductive approach will be used, and the implementation framework CFIR will guide the analysis in the first step.^50^ Thereafter, an inductive analysis will be used to describe the HCWs and the implementation of team members’ and managers’ experiences of the multifaceted intervention strategy for safe PHM with regard to the CFIR constructs in greater depth. Data from activity logs will be compiled and processed qualitatively and quantitatively.

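### The safety-climate hypothesis has two primary measures and two unranked time points against a single limit of 0.05, although the trial was powered for one NOSACQ-50 test

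*Protocol article*

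**What the plan says.** All places are in the protocol article.

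- **Table 1 (Outcome measures)** puts five measures under the primary heading. NOSACQ-50 and a research-specific PHM safety questionnaire come under intervention effectiveness. The acceptability, appropriateness and feasibility questionnaires (AIM, IAM, FIM) come under implementation outcome. All five are collected at both 4 months (T1) and 12 months (T2).
- **Primary outcomes (Intervention effectiveness)** says of NOSACQ-50: "This comprises 50 items across seven safety climate dimensions in the workplace". It names no single summary score. It then says: "An additional 14 specific research-based questions to evaluate the safety climate for PHM will also be used".
- **Design** describes a hybrid trial "where clinical effectiveness and implementation outcome are given equal priority".
- **Aims and hypothesis** states two separate between-arm hypotheses. One is a better safety climate in relation to PHM in arm A. The other is that the arm A strategy is seen as more acceptable, appropriate and feasible.
- **Data analysis and statistics** bases the power calculation on NOSACQ-50 only: "A power level of 0.8 (80%) and alpha of 0.05 was used". Linear mixed models for repeated measures will estimate "Potential differences between the intervention arms regarding primary outcome at 4-month and 12-month follow-up". One general rule follows: "The limit for statistical significance will be set at α=0.05". The section names no leading time point, no order among the measures and no rule for combining them.

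**The concern.** The effectiveness hypothesis is about one thing, safety climate in relation to PHM, but the article gives it two primary instruments and two follow-up times. If all four comparisons are read at 0.05, a significant result on either instrument at either time could be reported as confirming it. The type I error for that claim is then above the 5% at which the trial was planned. Which instrument or time point carries the headline could also be settled after the results are known.

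The same applies, separately, to the implementation hypothesis: three questionnaires at two time points, with no stated rule on how many must favour arm A, or when.

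**Working it through.** **1. The plan's own figure.** Inputs from Data analysis and statistics: "calculated minimum detectable change of 0.7 with an SD of 0.5 and within cluster correlation of 0.7", power 0.80 and alpha 0.05. The result given there is "at least six care units (clusters) for each arm with a minimum of 15 participants in each care unit". Sidedness is not stated; two-sided is assumed because it reproduces the stated number.

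- Participants per arm without clustering: 2 × [0.5 × (1.960 + 0.842) / 0.7]² = 8.01
- Design effect: 1 + (15 − 1) × 0.7 = 10.8
- Clusters per arm: 8.01 × 10.8 / 15 = 5.77, rounded up to 6
- Power with 6 clusters per arm (normal approximation): 81.5%

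So six units per arm is the size for **one** test at 0.05, with nothing set aside for a second measure or time point.

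**2. Counting the tests by hypothesis.**

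- Safety climate: 2 measures × 2 time points = 4 tests
- Safety climate, if NOSACQ-50 alone is the lead measure: 1 × 2 = 2 tests
- Implementation: 3 measures × 2 time points = 6 tests

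**3. Chance of at least one false positive when each test uses 0.05.** For k independent tests this is 1 − 0.95^k:

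- k = 2: 1 − 0.9025 = 9.75%
- k = 4: 1 − 0.8145 = 18.5%
- k = 6: 1 − 0.7351 = 26.5%

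The scales and repeated measurements will be positively correlated, which lowers these figures. The article gives no correlations, so a range is assumed. The results below are for two-sided normal tests with equal pairwise correlation, computed by numerical integration.

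| Tests | Independent | 0.5 | 0.8 | 0.9 |
|---|---|---|---|---|
| 2 (NOSACQ-50, two times) | 9.8% | 9.1% | 7.8% | 7.0% |
| 4 (two effectiveness measures, two times) | 18.5% | 15.6% | 11.4% | 9.4% |
| 6 (AIM, IAM, FIM, two times) | 26.5% | 20.7% | 13.9% | 10.8% |

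No entry is at or below 5%.

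**4. Cost of splitting alpha instead of ranking.** A Bonferroni split over just the two NOSACQ-50 time points (0.025 each) would lower normal-approximation power with six clusters per arm from 81.5% to 73.1%. Restoring 80% would take 6.98, so 7, clusters per arm. Naming one test keeps the planned size.

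**The case against.** **An unseen analysis plan may settle this.** Multiplicity procedures are often left to the statistical analysis plan, and a journal article is condensed. That is fair, and the absence of a named procedure is not the point here. The point is what the article does fix: several measures under the primary heading, two unranked time points, one limit of 0.05 and power for one test. A later plan could resolve this, but the article's choice of primary outcomes would still have to be brought into line with it.

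**NOSACQ-50 may already be the lead outcome.** The analysis section uses the singular for the primary outcome, powers only NOSACQ-50, and speaks of estimates with confidence intervals. This reading is reasonable and narrows the problem to two tests, but two time points still give 7% to 10%. A joint test over both times would avoid that; the article neither states one nor excludes it.

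**The implementation hypothesis is worded as a conjunction.** Read literally, all three of acceptability, appropriateness and feasibility must hold, and then no correction across the three is needed. This stands in part: the wording suggests such a rule but does not state it, and the time point stays open.

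**Stronger readings that a reader might infer.** One could pool all five measures at two times into 10 tests (40.1% if independent). Abstract and Aims keep effectiveness and implementation apart, and equal priority for two questions does not make success on either one a success of both. AIM, IAM and FIM cannot show a better safety climate. One could also count the seven NOSACQ-50 dimensions separately, giving 22 tests (67.6% if independent). The article describes the dimensions as the structure of the instrument and nowhere says they will be tested one by one. Neither figure describes the plan.

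**Conclusion.** The concern holds in a limited form. If any of the two effectiveness measures at either time point can support the safety-climate claim, its false-positive chance is about 9% to 19% instead of 5%. With NOSACQ-50 alone at both times it is about 7% to 10%. The implementation family, taken by itself, runs at about 11% to 26% unless all three measures must succeed at one named time point.

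These ranges rest on assumed equal correlations from 0.9 down to 0, on two-sided tests, and on the time points being tested separately. The inflation is moderate and does not undermine the design. It is worth removing because the remedy is a matter of wording and agrees with the single test for which the trial was sized.

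**What to change.** Before outcome data are seen:

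1. Name one NOSACQ-50 summary score at one time point as the only primary effectiveness test, at 0.05. The choice is the authors'; 12 months, the end of the study period, is a natural one.
2. Place the other time point, the PHM score and any dimension scores after it, either in a fixed order or with Holm's procedure.
3. Treat AIM, IAM and FIM as a separate family at one stated time point. Either require all three to be significant, as the wording of the hypothesis suggests, in which case no correction among them is needed, or apply Holm across the three.

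The change is confined to protocol or analysis-plan text. It needs no additional care units, because six per arm was calculated for one NOSACQ-50 test at 0.05. The downside is that fewer results can be called primary successes. In particular, the PHM-specific questions, which lie close to the stated hypothesis, would become supporting evidence.

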### Procedure

As a first step, the manager will sign an informed written consent form before the care unit’s participation in the study. All recruited care units willing to participate will be simultaneously randomised to either arm A or arm B by a computer-generated randomisation list. Stratification will be made in blocks by the size of the unit (large or small) and type of organisation (regional or municipal healthcare). Furthermore, care units in the same municipality and within the same regional healthcare departments will also be a factor in the stratification. The randomisation will be performed by an independent statistician prior to the baseline measurement in order to be able to adjust the planning and information to the care units belonging to arm A or arm B. The recruitment of care units and the randomisation into two intervention strategies (A and B) are presented in figure 1. The 12-month study period starts February 2023 and is divided in two phases. The first 4 month is classified as the active implementation period. In the following 8 months, the care units will continue to apply the intervention strategy.

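### The primary model names age and working experience, worded as baseline differences, but not the unit size and organisation strata used to randomise; fix both sets of covariates in advance

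*Protocol article*

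**What the plan says.** On allocation, the Procedure section of the protocol article says: "Stratification will be made in blocks by the size of the unit (large or small) and type of organisation", the two types being regional and municipal healthcare. It adds a third factor: "care units in the same municipality and within the same regional healthcare departments will also be a factor in the stratification". Data analysis and statistics restates only the first two: "Two predetermined conditions were taken into consideration in the randomisation, size of cluster and regional or municipal healthcare".

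On analysis, the same section says that arm differences in the primary outcome at 4 and 12 months "will be estimated using linear mixed models for repeated measures". It then gives the covariates: "The models will be adjusted for possible confounders (baseline differences concerning age and working experience"). No stratification factor appears among them. The section does not say whether the baseline NOSACQ-50 score, which Table 1 shows is collected at T0, enters the model.

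The sample size rests on "a calculated minimum detectable change of 0.7 with an SD of 0.5 and within cluster correlation of 0.7", with 80% power, alpha 0.05, and at least six units per arm with at least 15 participants each.

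**The concern.** There are two separate issues.

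The first is the missing strata. Stratified allocation balances unit size and organisation type between arms, so their effect drops out of the true variance of the arm contrast. A model without them still counts that variation as error. The standard error is then too large, the test is conservative, and power is lost in a trial of about twelve units. At the plan's correlation almost all the variance of a unit mean lies between units. Age and experience measured on individuals can therefore recover little precision, apart from any difference in their unit averages.

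The second is the stated reason for adjusting. In a randomised comparison, covariates are best fixed in advance because they predict the outcome. The bracketed wording refers instead to differences at baseline, and so leaves open whether age and experience enter in any case or only if the arms turn out to differ.

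**Working it through.** **Inputs from Data analysis and statistics:** difference 0.7, SD 0.5, within-cluster correlation 0.7, 15 per unit, 6 units per arm, alpha 0.05 (taken as two-sided), power 80%. **Assumed, because the article gives no figure:** R², the share of between-unit variance explained by size and organisation type together.

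**1. The plan's own figure.** Design effect = 1 + (15 − 1) × 0.7 = 10.8. Under individual randomisation, n per arm = 2 × (0.5 × (1.960 + 0.842) / 0.7)² = 8.01. Then 8.01 × 10.8 / 15 = 5.77, rounded up to 6 units per arm. The stated size reproduces, with normal-approximation power of 81.5%.

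**2. Where the variance lies.** Between-unit variance = 0.7 × 0.25 = 0.175. Within-unit variance of a mean of 15 = 0.3 × 0.25 / 15 = 0.005. The variance of a unit mean is 0.180, and 0.175 / 0.180 = 97.2% of it is between units.

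**3. Follow-up comparison of unit means, formula.** Without strata: SE = √(2 × 0.180 / 6) = 0.245, 10 df, 95% half-width 2.228 × 0.245 = 0.546, power 73%. With two binary strata terms: variance 0.175 × (1 − R²) + 0.005, 8 df, t = 2.306.

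| R² | Half-width with strata | Change from 0.546 | Power with strata |
|---|---|---|---|
| 0 | 0.565 | +3.5% | 71% |
| 0.1 | 0.537 | −1.7% | 75% |
| 0.2 | 0.507 | −7% | 80% |
| 0.3 | 0.475 | −13% | 84% |

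The widths are equal when 0.175 × (1 − R²) + 0.005 = 0.180 × (2.228 / 2.306)² = 0.168, that is, at R² of about 0.07.

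**4. True size, by simulation.** Twelve units were randomised within perfectly balanced strata, 40,000 runs per scenario.

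| R² | True size without strata | Power without | Power with |
|---|---|---|---|
| 0.1 | about 4% | 73% | 75% |
| 0.2 | about 3% | about 73–74% | about 80% |
| 0.3 | about 2% | 74% | 84% |

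With the strata in the model, size stayed at about 5% throughout.

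**5. If T0 is a model occasion.** Assume strata effects constant over time, R² = 0.2, and 70% of the remaining between-unit variance stable. The varying part is 0.175 × 0.8 × 0.3 = 0.042 per occasion, so the variance of a unit's change is 2 × (0.042 + 0.005) = 0.094. SE = √(2 × 0.094 / 6) = 0.177. The half-width is 2.228 × 0.177 = 0.394 without strata and 2.306 × 0.177 = 0.408 with them. In simulation the mean half-widths were 0.385 and 0.396, about 3% wider with the strata, and the unadjusted test had size 5.0%. At R² = 0.3 they were 0.362 and 0.372. In this setting the strata effects cancel from the contrast and only the cost in degrees of freedom remains.

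**The case against.** Several objections have force.

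- **The gain is not guaranteed.** No passage says how strongly size and organisation predict safety climate. Below an R² of about 0.07 the adjusted interval is no shorter, and if T0 is modelled with constant strata effects it is slightly wider. This stands. A reader might infer that the planned intervals are needlessly wide whatever happens; the article does not support that.
- **The gain depends on the plan's correlation of 0.7.** At 0.1 to 0.2, simulated power for 0.7 exceeds 98% with or without the strata. This also stands.
- **The covariates are named in advance.** The article gives no test or threshold for entry, so the sentence may simply mean adjustment for age and experience. A reader might infer that it invalidates the nominal error rate. The article does not support that either. In a simulation where an individual covariate entered only if the arms differed at p < 0.05 (assumed to explain 5 to 20% of within-unit variance, with its own correlation 0.05), true size was 4.9 to 5.0%. The strata omission errs in the conservative direction.
- **Adjusting for individual characteristics has a purpose here.** Units are randomised before baseline, workers consent before answering questionnaires, and the cohort is open to new employees. Composition can therefore differ by arm for reasons other than chance. This is a reason to keep age and experience in the model, and to keep them there unconditionally.
- **An article may leave the full covariate list to an analysis plan.** That is fair for silence. This article, however, states a covariate set and a rationale for it, and omits the factors it randomised by.

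**Conclusion.** The point holds as a specification weakness with a conditional cost. The stated adjustment leaves out both restated stratification factors, and its wording does not settle whether age and experience always enter.

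If the primary contrast compares follow-up levels and the strata explain 10 to 30% of between-unit variance, true size is about 4 to 2% rather than 5%, and power for 0.7 is about 73 to 74% where adjustment would give 75 to 84%. If they explain nothing, adjusting costs about 2 points of power (73% to 71%) and widens the interval by about 3.5%. If T0 is a model occasion and strata effects are constant, it costs about 3% in width. The possible gain is much larger than the possible loss, so the strata should be in the model.

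These figures rest on the plan's SD and correlation, 12 units of 15, two-sided testing, balanced strata and the assumed R². They do not show an inflated false-positive rate or a biased estimate.

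**What to change.** State the primary model's covariates in advance:

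- Unit size stratum and organisation type as fixed effects.
- Baseline NOSACQ-50, saying how it enters: T0 as a model occasion, or as individual and unit-mean covariates.
- Age and working experience, included regardless of observed imbalance. Remove the reference to differences at baseline as a criterion.
- For the acceptability, appropriateness and feasibility measures, which Table 1 collects only at T1 and T2, include the strata without a baseline term.
- Say how the third stratification factor (shared municipality or regional department) is handled. With about 12 units it would use too many degrees of freedom as fixed effects, so it need not be one, but the choice should be stated. The two accounts of the stratification, in Procedure and in Data analysis and statistics, should also be brought into line.

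The cost is wording and two cluster-level degrees of freedom, plus one more if a unit-mean T0 covariate is used. No new data are needed: the strata are known for every unit from randomisation, and the baseline questionnaire collects the rest.

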### Ethics and dissemination

Ethics approval was received from the Swedish national ethical board (Dnr 2021–00578). HCWs working in participating care units will provide informed consent to participate in the study. It will not be possible to identify any individual study participants when the results are presented. All data in paper form, such as questionnaire responses, informed consents, code keys and transcribed interviews, will be handled by the research group with confidentiality and stored in a safe space at the research group organisation. A code list will be drawn up and stored separately from the data in a locked cabinet to which only people in the research group who are employed by Region Östergötland have access. Moreover, the results and characteristics of participating individuals will be presented at the group level or in such a way that individuals cannot be identified. A data management plan will also be established, and all materials will be archived in accordance with current legislation and local procedures. A data monitoring committee was not needed as this is not a clinical trial with a sponsor.
